#### Acceptability and Usability of Intervention

Responses to the Likert items of the system usability scale are processed so that the total score ranges from 0 to 100. Empirical and validation studies suggest that systems scoring above 68 should be considered to have an above average usability [61]. We will calculate mean total scores and compare against this general guideline of 68.

To further investigate how different individuals perceive the usability of the intervention, linear regression models will be used to regress system usability scores against baseline characteristics and alcohol- and mediator-related outcome measures, as well as usage statistics of the intervention (collected as participants engage with the intervention).

#### Exploratory Analysis

The weekly assessments of the intervention group are primarily an aid for the individual to his or her behavior change. The data cannot be used in the primary analysis as they will quite certainly contain a lot of missing data (we do not expect participants to zealously report each week) and there are no data from controls. However, the data collected may nevertheless be useful to identify trends in potential reduction of alcohol consumption over time, thus, exploratory time series models will be created to see if there are patterns that are informative about intervention effects (such as reduction plateaus). Similarly, we will regress alcohol consumption outcomes on usage statistics in the intervention group, including frequency of use of different modules and whether or not the participant decided to stop the intervention before the end of the trial, possibly identifying a dose-effect relationship.

As part of the primary investigator’s precision health initiative, we aim to include predictive modelling of the intervention. Traditionally, trials contrast the mean difference between 2 groups; however, they do not address individual variability. Intuitively, we know that some individuals will respond well to an intervention, whereas others might not, and some might further be harmed by it. We wish to predict how individuals will respond to an intervention using only individuals’ baseline characteristics. We do this by measuring characteristics at baseline related to the behavior change theory, in this particular case self-efficacy, importance, and know-how, as well as alcohol consumption levels and conventional baseline characteristics (age and gender). These characteristics are then used to learn statistical models that predict individual outcomes.

Predictive analysis requires a radically different approach of assessing a model’s performance, as explaining and predicting are 2 different tasks [62]. We utilize a Bayesian approach using shrinkage priors [63,64], which allows us to include all characteristics measured at baseline and then learn which ones should be included in the predictive model from the data. The result is a model that can tell individuals how likely it is that the intervention has a positive effect on them specifically, rather than always quoting the group mean difference.

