## Introduction

### Background

Harmful use of alcohol contributes to approximately 4.5% of deaths globally, as well as having a causal relationship with a range of mental and behavioral disorders [1]. Premature death is not the only negative consequence from harmful alcohol use but it may also lead to injuries, road traffic accidents, violence, and social and economic burdens [2]. Not only does harmful drinking have consequences for the individuals consuming at increased levels but it may also result in a range of negative consequences for their family members and friends.

In Sweden, risky drinking is defined as either drinking more than 9 (female) or 14 (male) standard units of alcohol per week (weekly consumption) or drinking more than 4 (female) or 5 (male) standard units of alcohol on a single occasion at least once a month (heavy episodic drinking). A standard unit is defined as 12 g of alcohol in Sweden. These criteria vary among countries, where for instance the National Institute on Alcohol Abuse and Alcoholism in the United States uses the same thresholds except for a 7-unit threshold per week for women, but at the same time also defines 1 standard unit as 14 g of alcohol. A recent report showed that, in 2016, approximately 31% of the adult Swedish population were risky drinkers according to the Swedish criteria [3].

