
At any time, participants can send an SMS message with the word STOP to the phone number from which they receive messages. At this point, there will be no more SMS messages sent to the participant, including weekly assessments and links to the dashboard. Participants will, however, receive 1 more message where it says that we have acknowledged that they no longer wish to receive the intervention, unless they respond with START in an SMS, and that we will contact them solely with follow-up questionnaires, as previously agreed. The 4-month period of study for this trial is for research purposes only as, in principle, there is no finite end point to the intervention, and in a real-world setting, participants could engage with the intervention as long as they prefer. Therefore, we do not strictly interpret a STOP message from a participant as noncompliance but rather that the individual has decided that they no longer need the support. In an exploratory analysis, we will investigate if there is a relationship between alcohol outcomes and those who decide to stop the intervention before the 4-month mark.

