#### Recruitment and Eligibility

Using Web search engine advertisements (Google, Yahoo, and Bing) and social media (Facebook), we will target individuals in the general population of Sweden seeking help to reduce their alcohol consumption (advertisements are shown in Figure 2). Participants will initially be recruited over a 6-month period. Additional 6-month periods will be added if not enough participants have been recruited according to the initial power calculation. If 20.03% (426/2126) or less of the required population has been recruited at 12 months, then recruitment will stop at this time and data will be analyzed to inform future trial design. Recruitment will stop after 24 months if not before.

Individuals interested in participating in the study will be asked to send an SMS message with a specific code to a dedicated phone number. Within 10 min, participants will receive an SMS with a hyperlink that takes them to a Web page asking for informed consent. Individuals will be randomized to 1 of 2 different means of presenting the trial procedure when asking for informed consent (Consent-1 and Consent-2). Please see Multimedia Appendix 1 for more details.

All individuals giving informed consent will be asked to complete a baseline questionnaire, which will also assess eligibility for the trial. The inclusion criteria will include the following: aged 18 years or older, ownership of a mobile phone, and being classified as a risky drinker according to Swedish guidelines.

Note that there is no upper limit to alcohol consumption as an exclusion criterion, meaning the study population is anticipated to comprise both harmful (ie, individuals who have experienced harm from any level of consumption [48]) and hazardous drinkers (ie, individuals with a consumption pattern that suggests increased risk to health [48]). No additional support will be offered to individuals who have a very high-consuming behavior.

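### The one-arm weekly series is to be read for intervention effects such as plateaus, but selection at entry and selective reporting can give a fall and levelling-off with no effect (minor)

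*Protocol article*

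**What the plan says.** The Exploratory Analysis section first limits the weekly assessments: "The data cannot be used in the primary analysis as they will quite certainly contain a lot of missing data", "and there are no data from controls". It also notes that "we do not expect participants to zealously report each week". It then gives the same data a second use: "exploratory time series models will be created to see if there are patterns that are informative about intervention effects (such as reduction plateaus").

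Three other parts of the protocol article bear on this:

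- **Entry.** Recruitment and Eligibility requires "being classified as a risky drinker according to Swedish guidelines", and the advertisements target people who want help to cut down. Background defines risky drinking as "drinking more than 9 (female) or 14 (male) standard units of alcohol per week (weekly consumption") or, alternatively, at least monthly heavy episodes. Measures confirms that either criterion is enough. Weekly consumption is judged on the previous week and heavy episodes on the previous month.
- **End of reporting.** Under Intervention Content, after a STOP message "there will be no more SMS messages sent to the participant, including weekly assessments and links to the dashboard". The protocol reads STOP as a decision that support is no longer needed. Follow-up questionnaires continue.
- **The protocol's own principle.** Control Conditions states that an effect estimated in a randomised trial has meaning only relative to the control condition.

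**The concern.** A trend in one arm mixes any intervention effect with whatever would have happened anyway. Here two features of the design can shape that trend.

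First, people enter when their recent drinking is above a threshold and when they have decided to seek help. Later weeks tend to drift back toward each person's usual level and then flatten. That is the kind of pattern the plan names.

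Second, the people who report change from week to week. Some skip and some send STOP. If lighter drinkers leave, the mean among reporters rises; if heavier drinkers leave, it falls. The document does not tell us which to expect.

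The plan recognises the missing data and the missing controls, but uses them only to keep the series out of the primary analysis. The following sentence still links the pattern to intervention effects. At stake is a secondary conclusion about how quickly the effect sets in and when it levels off.

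**Working it through.** **The plan's own figures.** The protocol gives no figure for the weekly analysis. The yardstick is the 15% reduction assumed in Power Calculation. That calculation reproduces: averaging two-sided Wald power over the stated distributions, with SE² = (1/μ_I + 1/θ)/n_I + (1/μ_C + 1/θ)/n_C, gives 0.791 at N = 1800 against the stated 0.79.

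**Inputs from the protocol.** Weekly thresholds are more than 9 units (women) or 14 (men). Heavy-episode thresholds are more than 4 or 5 units on one occasion, over the past month. Either criterion suffices.

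**Inputs assumed, not in the protocol.** Half the pool is male and the mean before selection is 8 units a week. Weekly intensity is lognormal with squared coefficient of variation 1, so the log-scale variance is s² = ln 2 = 0.693. The heaviest day carries 45% of the week's units. A share r of s² (0.3 to 0.9) is stable between persons. The remainder is independent from week to week or autoregressive with coefficient 0.5 or 0.8.

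**Model, with no intervention effect.** Units in week t are Poisson with mean exp(ln 8 − s²/2 + p + √(s²(1−r))·e_t), where p has variance r·s² and e_t has variance 1. A person enters if week 0 exceeds the weekly threshold, or if 0.45 × units exceeds the heavy-episode threshold in any of weeks −3 to 0. There were 400,000 simulated persons per scenario.

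**Results, entry on either criterion** (percentages from unrounded means):

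| Weeks within person | r | Baseline | Week 1 | Week 8 | Week 16 | Fall, baseline to week 8 | Fall, week 1 to 16 |
|---|---|---|---|---|---|---|---|
| Independent | 0.3 | 10.5 | 9.4 | 9.4 | 9.4 | 11% | −0.4% |
| Independent | 0.5 | 11.3 | 10.4 | 10.4 | 10.4 | 8% | −0.1% |
| Independent | 0.9 | 13.5 | 13.1 | 13.1 | 13.0 | 3% | 0.2% |
| AR 0.5 | 0.3 | 11.4 | 10.3 | 9.5 | 9.5 | 17% | 8.0% |
| AR 0.5 | 0.5 | 12.0 | 11.1 | 10.6 | 10.5 | 12% | 5.4% |
| AR 0.5 | 0.9 | 13.7 | 13.3 | 13.2 | 13.2 | 4% | 0.7% |
| AR 0.8 | 0.3 | 12.6 | 11.8 | 10.1 | 9.7 | 20% | 17.6% |
| AR 0.8 | 0.5 | 13.0 | 12.4 | 11.1 | 10.8 | 15% | 12.4% |
| AR 0.8 | 0.9 | 14.0 | 13.7 | 13.4 | 13.4 | 4% | 2.4% |

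For example, 1 − 10.6/12.0 = 12%.

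**Reading the table.** From baseline the mean falls in every scenario. With independent weeks the whole fall lies between baseline and week 1, and the weekly reports themselves are flat. With AR 0.5 the decline levels off by about weeks 4 to 8. With AR 0.8 it is still easing after week 8.

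**Not sized.** Help-seeking at entry and selective reporting were left out of these runs. The simulated pool is not calibrated to Sweden: 41% to 62% of it is eligible, against the 31% of adults quoted in Background, although respondents to the advertisements need not resemble the general population.

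**The case against.** The best case for the plan is that it already limits itself. The models are labelled exploratory, the wording is tentative, and the same paragraph admits that "there are no data from controls". People who send STOP still receive the follow-up questionnaires, and stopping is to be examined against outcomes. All of this stands, and it keeps the weight low. It does not make an uncontrolled trend informative about an effect.

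Four stronger readings are tempting, and the document does not support them:

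- **That a fall and plateau must appear.** The section models the weekly assessments and does not say that the baseline questionnaire belongs to the series. Without baseline, and with independent weeks, selection leaves the series almost flat. Some carry-over is still possible, because the first Sunday report asks about the past week and its window can overlap the baseline week.
- **That the artefact is 16% to 46%.** Those figures need entry on weekly units alone. They also need the power calculation's mean of 10, which already describes risky drinkers at follow-up, to be treated as an unselected mean and cut at the threshold again. The protocol's rule is either criterion.
- **That a plateau would be used to set how long the programme runs.** Nothing says so. Intervention Content and Principal Findings leave duration to the user.
- **That the trial's main result is at risk.** The randomised comparison does not use these data.

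**Conclusion.** The concern holds as a minor point. The weekly series cannot separate an intervention effect from return to usual drinking, from change that help-seekers would have made anyway, or from a shifting set of reporters. The phrase that ties it to intervention effects conflicts with the protocol's own statement that effects are relative to control.

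Under the either-criterion rule, the no-effect fall is about 3% to 20% from baseline to week 8. From the first weekly report to week 16 it is about 0% to 18%, and near zero with independent weeks. The upper part of each range reaches the planned 15%. Both ranges rest on assumed week-to-week variability and an assumed drinking distribution, so they show what can happen and do not predict this trial's data. The primary estimate, its power and the randomised inference are unaffected.

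**What to change.** In Exploratory Analysis, replace the wording about intervention effects with a description of within-arm change in reported drinking among those who report, starting at the first weekly report. State that this start reduces the carry-over from selection at entry but may not remove it.

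Take any statement about effect over time from the randomised data. Fit a repeated-measures negative binomial model to 2- and 4-month weekly consumption in both arms, with arm, time and arm-by-time terms. It shows whether the effect grows, holds or fades between the two points. It cannot locate a plateau, and the text should say so.

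The cost is a wording change and one extra model on data already being collected. What is lost is weekly resolution for claims about effect, which an uncontrolled series cannot supply.

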#### Intervention and Control Conditions

Eligible individuals will be randomized to either an intervention group or a control group (intervention and control). The intervention group will receive the novel intervention for 4 months and will also be recommended to read about alcohol, health, and society on the same website as the control group (see Multimedia Appendix 2). Participants allocated to the control group will be advised that they will go through an initial phase of 4 months during which they are to receive information to increase their motivation and reduce their consumption, after which they will be given access to the new support tool. Thus, individuals allocated to the control setting will be given access to the novel intervention after completion of the final follow-up (4 months after randomization); no further data will be collected from individuals in the control setting.

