**Main Hypotheses**
1. Alcohol consumption will differ between intervention and control groups, with the intervention group drinking less than control at 2 and 4 months after randomization. The 2-month interval will be primary.2. Confidence, importance, and know-how at 1-month follow-up will mediate the effects of the intervention on drinking outcomes at 2-month follow-up. The same measures at 2-month follow-up will mediate the effect on drinking outcomes at 4-month follow-up.3. Enrollment rates will differ between groups Consent-1 and Consent-2.4. Accurate recall of study parameters will differ between groups Consent-1 and Consent-2.5. Rates of accessing further information will differ between groups Info-1 and Info-2.

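### The exploratory regression of drinking on app usage and STOP status should not be offered as possible dose-effect evidence: stopping can follow from drinking, and up to half its window falls after the 2-month outcome

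*Protocol article*

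**What the plan says.** Under Exploratory Analysis, the protocol article states that "we will regress alcohol consumption outcomes on usage statistics in the intervention group, including frequency of use of different modules", together with "whether or not the participant decided to stop the intervention before the end of the trial, possibly identifying a dose-effect relationship". This is a comparison inside one randomised arm.

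Intervention Content describes the same STOP analysis as a search for a relationship between alcohol outcomes and "those who decide to stop the intervention before the 4-month mark". It also says how a STOP message is to be understood: not strictly as noncompliance, but "rather that the individual has decided that they no longer need the support". The dashboard modules are open to participants in any order and as often as they like.

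Intervention and Control Conditions gives the length of exposure: "The intervention group will receive the novel intervention for 4 months". Main Hypotheses sets the outcome times, "with the intervention group drinking less than control at 2 and 4 months after randomization", and adds "The 2-month interval will be primary". Measures sets the recall periods: last week for total consumption and the past month for heavy episodic drinking.

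**The concern.** A dose-effect reading needs the dose to come before the response, and the dose must not itself be driven by the response. The stated definitions put both conditions in doubt.

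- **Timing.** A participant who sends STOP in month 3 counts as a stopper. If that status is used to explain drinking at month 2, the exposure comes after the outcome.
- **Direction.** If people stop because they have cut down, lower drinking causes stopping. If others stop because they have given up, higher drinking causes stopping. Either way the regression can return an association when usage does nothing, and its sign reflects why people disengage.

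At stake is an interpretive claim, not the trial's main result. The Discussion stresses that users choose how long they use the tool, so a dose-effect statement would bear directly on advice about continued use. Statistical Analysis Methods also applies two-tailed 5% tests to coefficients of interest in all models, so a spurious association could be reported with a P value.

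**Working it through.** The protocol states no figure for this analysis, so there is none to reproduce. The check has two parts.

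**1. Timing.** The STOP window is months 0 to 4, and the primary outcome is at month 2. The share of the window after that outcome is (4 − 2)/4 = 0.5. For the 4-month outcome it is (4 − 4)/4 = 0, although stops in the last week or month still overlap that outcome's recall period.

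**2. Size of a spurious association when usage has no effect.**

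Inputs from Power Calculation:
- 1800 analysed in total, so about 900 in the intervention arm;
- control mean 10 units and a 15% reduction, so an intervention mean of 10 × 0.85 = 8.5;
- negative binomial dispersion θ = 1.

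As a check on these inputs, averaging Wald power over the stated priors gives 0.787 at N=1800, against the stated 0.79.

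Assumptions that the protocol does not give: about 30% stop, all after month 2; high drinkers are those above 6 units at month 2 (roughly the upper half); the odds ratio (OR) of stopping, high versus low, is varied. There is no adjustment for baseline drinking.

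With θ = 1 the counts are geometric, so the expected result can be written down:
- P(high) = (8.5/9.5)^7 = 0.459.
- Mean if high = 7 + 8.5 = 15.5. Mean if low = (8.5 − 0.459 × 15.5)/0.541 = 2.56.
- Stopping odds = (0.3/0.7) × √OR for high drinkers and (0.3/0.7)/√OR for low drinkers.

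For OR = 0.5:
- P(stop) is 0.233 if high and 0.377 if low.
- Overall P(stop) = 0.459 × 0.233 + 0.541 × 0.377 = 0.311.
- Mean in stoppers = (0.459 × 0.233 × 15.5 + 0.541 × 0.377 × 2.56)/0.311 = 7.00. By the same steps, the mean in non-stoppers is 9.18.
- Rate ratio = 7.00/9.18 = 0.76.
- SE of the log ratio = √[(1 + 1/7.00)/(900 × 0.311) + (1 + 1/9.18)/(900 × 0.689)] = 0.077.
- z = ln(0.763)/0.0766 = −3.5, so rejection is about Φ(3.52 − 1.96) = 94%.

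Simulation (400 runs per row, negative binomial regression of 2-month drinking on STOP status) against this formula:

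| OR of stopping, high vs low | Rate ratio, simulated | Rate ratio, formula | Rejection, simulated | Rejection, formula |
|---|---|---|---|---|
| 1.0 | 1.00 | 1.00 | 5% | 5% |
| 0.8 | 0.92 | 0.92 | 21% | 20% |
| 0.67 | 0.86 | 0.86 | 50% | 52% |
| 0.5 | 0.76 | 0.76 | 93% | 94% |
| 1.5 | 1.17 | 1.16 | 51% | 49% |
| 2.0 | 1.29 | 1.28 | 90% | 90% |

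At an odds ratio of 0.67 or 1.5, the spurious ratio is already about as far from 1 as the 15% effect the trial is powered for.

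**The case against.** The strongest reply is that the protocol has already made the concession. The analysis is headed exploratory, the dose-effect phrase is hedged as a possibility, and Intervention Content asks only about a relationship while giving the benign reason for stopping. The text also never says outright that 4-month STOP status will be paired with the 2-month outcome. Pairing it with the 4-month outcome is a natural reading, and usage windows for an exploratory model may be set in a fuller document that is not shown.

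Much of this stands, and it limits the point. A reader might infer that the protocol will treat any usage association as an established dose-effect, or that the analysis would almost always produce one. The documents support neither. The wording is tentative, and the rejection rate runs from 5% to 93% across assumed odds ratios. If some stop because they improved and others because they gave up, the biases could partly cancel. A reader might also extend the no-longer-needed explanation to all usage, but the protocol gives it only for STOP messages. For module use, the documents show free choice and no stated time window.

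What does not fall away is the stated reading itself. The alcohol outcomes are named in the plural with no restriction to month 4, and the hypotheses make month 2 primary. The STOP window is stated, so this is not merely missing detail. A hedge does not make a dose-effect interpretation sound when the same document says that "the individual has decided that they no longer need the support" may be why people stop.

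**Conclusion.** The point holds as a minor one. Followed as written, the plan can use stopping after the 2-month outcome as an exposure for it. At either time point it offers a self-selected and possibly reverse-causal association as potential dose-effect evidence. The timing part is conditional on the 2-month outcome being modelled. The reverse-causation part applies to both outcomes.

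With no usage effect, the spurious rate ratio lies between about 0.76 and 1.29 for stopping odds ratios between 0.5 and 2.0, and rejection rises from 5% at an odds ratio of 1.0 to 90% or more at the ends. These figures show the mechanism. They rest on the assumed 30% stopping, stopping after month 2, the assumed odds ratios and no baseline adjustment, so they do not predict this trial's result. The randomised intention-to-treat comparison is not touched.

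**What to change.** - For each outcome, count only usage and STOP messages before that outcome's recall period, using one landmark before the 2-month and another before the 4-month follow-up. Because recall is one week for total consumption and one month for heavy episodic drinking, the landmark may differ between the two outcomes.
- Adjust for baseline drinking, the three psychosocial items (confidence, importance, know-how) and, where available, drinking reported in earlier weekly assessments.
- Report the result as an association with engagement, state that reverse causation may remain, and remove the dose-effect wording so that Exploratory Analysis agrees with Intervention Content.

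The cost is one analysis definition and a few words; no data collection changes. There are two downsides. Usage after the landmark is not used for that outcome. The weekly assessments will have much missing data, as the protocol expects, and they end for anyone who sends STOP, so adjustment for earlier drinking will be incomplete. The landmark removes the timing fault but only reduces the reverse-causation bias, which is why the wording must change as well.

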### Design

To study the effect of the intervention, a 2-arm parallel group randomized controlled trial will be employed. Nested within this trial will be the 3 substudies.

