### Power Calculation

We conducted a Monte Carlo simulation study to determine the necessary number of individuals to randomize (N). We deliberately focused on the total weekly consumption outcome, as the analysis of this outcome in general requires more individuals than does the analysis of heavy episodic drinking (because of higher variance). We will begin by describing the initial distributional assumptions that we made and then the result of the simulations. We aimed to achieve 0.8 power at the .05 significance threshold.

The effect (γ) of the intervention, that is, the percentage reduction in mean total weekly alcohol consumption in the intervention group, is assumed to follow a beta distribution with mean 0.15 and SD 0.025.The mean number of standard units consumed in the control group (μ_C_) at follow-up is assumed to follow a normal distribution with mean 10 and SD of 0.5. The population under analysis are risky drinkers, thus, a mean consumption of 10 standard units is appropriate, and the analysis is quite robust to moderate changes in this assumption.The mean number of standard units consumed in the intervention group (μ_I_) at follow-up is assumed to follow a normal distribution with mean (1-γ)_C_ and SD of 0.5.The distribution over the number of standard units consumed at follow-up for both the intervention and control group is assumed to follow a negative binomial distribution. The means of these distributions are given by μ_C_ and μ_I,_ respectively, and have a dispersion parameter θ sampled from a normal distribution centered at 1 with an SD of 0.05.The number of individuals allocated to the intervention group follows a binomial distribution, with a 0.5 probability of success over N trials.

The Monte Carlo simulation explored different values of N (number of individuals randomized). For each N explored, the following simulations were done:

Draw 1 sample each for γ, μ_C_, μ_I,_ and θAllocate a random number of individuals to the interventionGive each individual a number of standard units consumed following the negative binomial distribution appropriate for their respective groupsAnalyze the data using negative binomial regressionNote if the 0.05 threshold has been broken for the group allocation coefficient in the regression modelRepeat 100 times from (a) and then calculate power as the percentage of times that the threshold was brokenRepeat 1000 times from (1) and calculate the average power from (e)

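### The exploratory predictive model is described as giving each person's own probability of benefit; this parallel-group trial identifies only average effects among people with the same baseline profile

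*Protocol article*

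**What the plan says.** The predictive modelling is described in the protocol article under Statistical Analysis Methods, Exploratory Analysis. Its premise is that response varies between people: "Intuitively, we know that some individuals will respond well to an intervention, whereas others might not, and some might further be harmed by it". Its aim is "We wish to predict how individuals will respond to an intervention using only individuals’ baseline characteristics". On method, the section says "These characteristics are then used to learn statistical models that predict individual outcomes", using a Bayesian approach with shrinkage priors to select among the baseline characteristics. The product is stated as a result: "The result is a model that can tell individuals how likely it is that the intervention has a positive effect on them specifically", and it is contrasted with the usual report by the words "rather than always quoting the group mean difference".

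The design that supplies the data is given elsewhere. Under Design, "a 2-arm parallel group randomized controlled trial will be employed". Under Intervention and Control Conditions, controls gain access to the intervention only after the 4-month follow-up, at which point "no further data will be collected from individuals in the control setting".

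**The concern.** Whether an intervention helps a given person depends on two outcomes for that person: consumption with it and consumption without it. In this trial only one of the two is ever recorded. Randomization identifies the distribution of each outcome, overall and within levels of baseline characteristics. It does not identify how the two are paired within a person. A probability of benefit for one individual is a property of that pairing, so neither a larger sample nor a different prior makes it estimable from these data.

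The sentence promises the person-specific quantity and distinguishes it from a group mean. What the data support is an average effect among people who share a profile, which is still a mean over a group, only a narrower one. What is at stake is what the exploratory analysis may conclude. A figure reported as a person's chance of benefit would rest on an unstated modelling assumption rather than on the trial.

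**Working it through.** **1. The plan's own figures.** The section Power Calculation states "We aimed to achieve 0.8 power at the .05 significance threshold" and reports average power of 0.79 at N=1800. Simulating its scheme (beta effect with mean 0.15 and SD 0.025; normal means with SD 0.5; negative binomial outcomes; dispersion around 1; simple 1:1 allocation; two-sided Wald test on the log mean ratio; 40,000 draws) gives 0.790. The expected loss comes out at 325 (interquartile range 231 to 399), against the stated 326 (231, 398). These figures reproduce and are not in question. They are used below only as planning values.

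**2. Inputs.** Control mean 10; intervention mean (1 − 0.15) × 10 = 8.5; dispersion θ = 1, all from Power Calculation. With θ = 1 the negative binomial is geometric, so with Y0 and Y1 the outcomes without and with the intervention:

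- F0(k) = P(Y0 ≤ k) = 1 − (10/11)^(k+1)
- F1(k) = P(Y1 ≤ k) = 1 − (8.5/9.5)^(k+1)

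Benefit here means Y1 < Y0, that is, drinking fewer units with the intervention than without it.

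**3. Sharp bounds on the share who benefit, given only the two distributions.**

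- Lower: max over k of [F1(k) − F0(k)]. The maximum is at k = 9: 0.6712 − 0.6145 = 0.057.
- Upper: 1 − max over k of [F0(k) − F1(k−1)]. The maximum is at k = 0: F0(0) = 1/11 = 0.091, so the bound is 0.909. Someone who would drink nothing without the intervention cannot drink less with it.

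**4. Specific pairings that give the same two arm distributions.**

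| Within-person link | Better | Unchanged | Worse |
|---|---|---|---|
| Rank-preserving | 72.9% | 27.1% | 0% |
| Independent | 51.3% | 5.1% | 43.6% |
| Rank-reversing | 51.3% | 2.8% | 45.9% |

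For the independent row, p0 = 1/11 and p1 = 1/9.5, so 1 − (1 − p0)(1 − p1) = 1 − 0.8134 = 0.1866. Then better = (10/11)(1/9.5)/0.1866 = 0.513, and unchanged = (1/11)(1/9.5)/0.1866 = 0.051. The trial data would look the same under every row, although the share made worse runs from none to nearly half.

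**5. Do baseline covariates close the gap?** The protocol gives no figure for how well baseline predicts follow-up, so this is an assumption shown over a range. Suppose that within a baseline profile the means stay at 10 and 8.5 and the residual spread shrinks, which raises θ:

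| θ within profile | Lower bound | Upper bound |
|---|---|---|
| 1 | 6% | 91% |
| 2 | 8% | 96% |
| 4 | 11% | 98% |
| 5 | 11% | 98% |
| 10 | 14% | 99% |

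The range stays wide throughout.

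**6. The quantity that can be estimated.** Take the overall mean ratio as an example, with 900 per arm and an observed ratio of 0.85. The standard error of the log ratio is √[(1/8.5 + 1)/900 + (1/10 + 1)/900] = 0.0496. Then −ln(0.85)/0.0496 = 0.1625/0.0496 = 3.27, and the probability that the mean effect favours the intervention is about 0.9995 (normal approximation, flat prior). This is a statement about a mean. At the same planning values the share of people who benefit is known only to lie between 6% and 91%, so the two quantities cannot stand in for one another.

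**The case against.** The strongest reply is that the section can be read so that the claim is sound. Prediction uses baseline characteristics only, so two people with the same profile receive the same figure. In a Bayesian model, the likelihood of a positive effect reads naturally as the posterior probability that the effect at that profile is favourable. The contrast would then be with the single overall trial difference. That quantity is estimable and may well be what the authors intend. This stands as to intent, but it does not rescue the wording: the sentence claims an effect on the person specifically and sets it apart from a group mean, and a profile-conditional mean is still a group mean.

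Three stronger readings are tempting, and the document does not support them.

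- A reader might infer that the model will be purely prognostic, predicting consumption rather than effect. The model terms are not given, and the analysis section for hypotheses 1, 6 and 7 already plans effect-modification tests in all models and slopes varying by age group. It does not say that these feed the predictive model, but nothing shows that the model omits them.
- A reader might infer that the plan validates the model against the wrong target. It states no validation target, only that predictive performance needs a different kind of assessment. That detail is commonly left to a fuller analysis plan.
- A reader might infer that drinkers would be steered towards or away from support by these figures. The text describes what the model is able to do. Nowhere does it plan to give predictions to participants or to use them to allocate support.

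**Conclusion.** The point holds in limited form. As written, the sentence attributes to the model a person-specific probability of benefit that this design does not identify. At the planning values, before conditioning on covariates, that probability is confined only to about 6% to 91%, and it remains wide (14% to 99%) even with θ assumed to be 10 within a profile.

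The non-identification follows from each person's outcomes being recorded in one arm only and does not depend on the planning values. The numerical bounds do: they assume negative binomial outcomes with means 10 and 8.5, and the within-profile versions rest on the assumed values of θ.

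Severity is low. The analysis is labelled exploratory and is worded as an aim. The trial's hypotheses, the primary adjusted models, the power calculation and the sample size are untouched.

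**What to change.** Restate the deliverable as the predicted average between-arm difference in consumption among people with a given baseline profile, with its credible interval. If a probability is wanted, report the posterior probability that this average favours the intervention, and label it as such. State that it is obtained from allocation-by-characteristic terms under the shrinkage priors already planned. Drop the wording that claims an effect on the individual specifically.

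As an optional addition, check how well the predicted between-arm difference is calibrated in data not used to fit the model. This would supplement the plan; it does not correct a stated rule.

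The cost is a rewording and a more modest claim. No new data, no change to the sample size and no change to the primary analysis are needed.
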